## Abstract

**Background:**

Mental well-being is poor in long-term care facilities (LTCF) residents. Physical disabilities, impaired social engagement, and environmental stress are also common in LTCF which exacerbate the decline of the mental well-being of older people living in LTCF. Protective elements, including nature-based, reminiscence, outdoor, and group activities, are known to be effective to promote the mental well-being of older people living in LTCF. However, limited by their physical disabilities and poor social support, older people living in LTCF are not likely to benefit from these effective measures. Virtual reality has been proven to be feasible to be environmentally unrestricted to providing LTCF residents with all protective elements promoting mental well-being. However, its effects on the mental well-being of LTCF residents living with physical disabilities are unclear.

**Methods:**

This study employs a single-blinded, two-parallel-group (intervention-to-control group ratio = 1:1), non-inferiority, randomized controlled trial. Eligible participants are aged 60 years or above, LTCF residents, and living with physical disabilities. The study will be conducted in LTCF. In the intervention group, participants will receive a 6-week VR experience program. In the control group, participants will receive the usual care provided by the LTCF. The primary outcome is mental well-being, as measured by World Health Organization Five Well-being Index at the time point of baseline (i.e., week 0) and after completion of the intervention (i.e., week 7). This study aims to recruit a total of 216 participants. Generalized estimating equations (GEE) will be used to examine the effects of the intervention.

**Trial registration:**

The trial has been registered at ClinicalTrials.gov (Identifier: NCT05818579), Registered on April 5, 2023. The latest version of the protocol was published online on 19 April 2023. All items come from the World Health Organization Trial Registration Data Set. This study has been approved by the Research Ethics Committee of Tung Wah College, Hong Kong (reference number: REC2023158). The findings will be disseminated in peer-reviewed journals, presented at international and local conferences with related themes, and shared in local media.

**Supplementary Information:**

The online version contains supplementary material available at 10.1186/s13063-023-07592-7.

## Introduction

### Background and rationale

Physical disabilities refer to a physical condition that limits a person’s capacity to participate in activities of daily living [1]. In the scenario that the family of older people living with physical disabilities are not able to take care of them, they usually end up living in long-term care facilities (LTCF). A study showed that the prevalence of physical disabilities is up to 62% [2]. Physical disabilities are also associated with a lower level of social engagement, including participation in social organizations, use of senior center activities, talks to friends, and even use of the internet [3]. Unsurprisingly, a systematic review showed that their mental well-being is poor and that the prevalence rates of loneliness and depression among older people living in LTCF are high (56.92.5% and 11–85.5%, respectively) [4]. Physical disabilities cause poorer mental well-being [5]. Social engagement is also positively associated with the quality of life in older people with physical disabilities [6]. The detrimental effect of lower social engagement in institutionalized older people living with physical disabilities on mental well-being and quality of life is further exacerbated by the social distancing policies during and after the COVID-19 pandemic [7, 8].

Mental well-being, as defined by WHO, is a state where people realize their abilities, can cope with the normal stress of life, can work productively, and can contribute to their community [9]. Mental well-being is associated with many health mental health symptoms, including depression and health-related quality of life [10, 11]. Loneliness has also been identified to be a risk factor for depressive symptoms, while social support is known to be a protective factor mediating the effect of loneliness on depressive symptoms [12]. Previous studies showed that social support interventions (e.g., video conference programs) are effective to reduce loneliness and depressive symptoms [13, 14]. However, a study showed that family members' acceptance rate of videoconferencing use was low because of various reasons, such as preferring other alternatives (e.g., hiring a private caregiver) [15]. Visitation is still a preferred option by family and the older people living in LTCF, however, a systematic review showed that there are many reasons hampering family visitation of residents in LTCF, including family-residents’ relationships, employment, finances, and travel time [16]. Albeit the fact that family involvement is known to be associated with improved quality of life, evidence showed that family could only spend 4–9 h per week on the residents in LTCF and the involvement tend to decrease as the resident’s length of stay increases [17]. These interventions depending on family members do not benefit older residents without family members or having minimal family involvement.

Nature-based activities refer to the purposeful use of nature to formulate therapeutic activities which have been used to promote the mental well-being of older people (e.g., alleviating depressive symptoms, and promoting subjective happiness) [18–20]. However, nature-based activities commonly demand large outdoor spaces. Even indoor garden activities, the level of participation of older people living with physical disabilities is still expected to be limited. Reminiscence therapy refers to activities assisting older people to review their past, thus resulting in helping the resolution of the last development stage known as “ego integrity vs despair” in older people as derived from Erickson’s Psychosocial Development Theory [21]. A systematic review showed that reminiscence therapy can reduce depression in older people in LTCF [22]. Environmental stressors, mostly unmodifiable, are known to be associated with mental well-being in older people and outdoor leisure activities protectively mediate the effect of environmental stressors on the mental well-being of older people, particularly in LTCF [23]. An early study showed that several environmental factors in LTCFs cause.

depression in older people, including loss of independence, loss of freedom and continuity with their past life, loneliness, lack of privacy, and loss of autonomy due to the institutional regimen and regulations [24]. Evidence supported that outdoor recreational activities are protectively associated with depression in older people. However, their disability and the post-COVID-19 residual social distancing policy hinder them to participate in outdoor recreational activities.

Virtual reality (VR) is a computer system which can immerse users in a virtual environment by replacing the visual and aural environments to achieve a sense of presence so that users perceive themselves as being part of the virtual environment [25]. VR, therefore, renders LTCF possible to be environmentally unrestricted to providing LTCF residents with all protective elements promoting mental well-being. In the literature, as shown in a recent systematic review, VR has been used to promote mental health in older people mainly in three areas, including testing, training, and screening [26]. For training purposes, evidence supports that VR is effective to reduce loneliness and depressive symptoms in long-term care settings [27, 28]. One of the major strengths of using virtual encounters is that it does not involve family members and the variety of virtual experiences is not limited by space and environment. VR has also been used as a medium to deliver many therapeutic interventions (e.g., motor-cognitive training, gardening, outdoor leisure activities, tourism, and reminiscence) that are effective to promote health (e.g., cognitive function, physical function, mental well-being), feasible, and acceptable by older people, even in those who have various types of vulnerable conditions [29–33].

The use of VR in promoting the health of older people in LTCF is gaining popularity and its effects on the mental well-being of vulnerable groups, such as cognitive impairment, have been observed. However, most of the studies demonstrated the feasibility and preliminary effects in small feasibility or pilot studies only [30–33]. There is a lack of well-designed randomized controlled trials with an adequate number of samples to provide convincing evidence of its effects on mental well-being. Furthermore, some other interventions employed the element of physical activity (e.g., exergaming) in the intervention that they cannot be tolerated well by older people with physical disabilities [34]. Also, in the past, VR was a single-player activity, which may not induce peer social support through co-participation among participants in LTCF. Albeit the fact that VR has potential effects to promote the mental well-being of older people in LTCF, the effects of VR experience employing therapeutic elements without physical training components on social support and mental well-being are unproven in the context of older people with physical disabilities, in a randomized controlled trial with a representable number of sample.

### Objectives

This study aims to examine the effects of the therapeutic VR experience in older people with physical disabilities in LTCF in (1) increasing mental well-being, (2) reducing depressive symptoms, (3) reducing loneliness, (4) increasing health-related quality of life, and (5) increasing perceived social support.

### Trial design

This study employs a single-blinded, two-parallel-group (intervention-to-control group ratio = 1:1), non-inferiority, randomized controlled trial.

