#### Groups

Participants allocated to the intervention group will participate in the 6-week VR experience program. Participants allocated to the control will receive the usual care provided by the LTCF, such as personal care, regular basic medical and nursing care, and social support activities, as committed by the Social Welfare Department [37].

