#### Relevant concomitant care

The participants allocated to the intervention group receive the same usual care provided by the LTCF. The research team does not interfere with the usual care provided to the participants in either group. However, participants are prohibited to participate in other additional activities related to VR experiences provided by other organizations during the intervention period.

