### Sample size

In the literature, there is a lack of randomized controlled trials evaluating the effect of therapeutic VR experience on mental well-being using specifically in older people with physical disabilities. A similar study evaluating the effects of feedback-based virtual reality exercise on mental health (measured by the mental component summary of the Short-Form Health Survey–36 items) in older women showed that the between-group effect size at the follow-up timepoint is moderate (i.e., *d*= 0.407) [49].

A priori power analysis using G*Power employing the statistical test of two-tailed *t*-test (means: difference between two independent means of two groups) is employed. We assume that The level of significance is set at 0.05. The effect size *d*is set at 0.407 [49]. The power is set at 0.8. The group allocation ratio is set at 1:1. It is estimated that 192 samples are needed with 96 samples in each group. Considering the attrition rate of 11.3% referring to another similar study examining the effects of a VR hands-on horticultural therapy on institutionalized older people [28], the total sample size of the proposed study is estimated to be 216.

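### The trial is labelled non-inferiority, but its objectives, comparator, sample size and analysis all pose a superiority question

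*Protocol article*

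**What the plan says.** The Trial design section consists of one sentence: "This study employs a single-blinded, two-parallel-group (intervention-to-control group ratio = 1:1), non-inferiority, randomized controlled trial". The Methods paragraph of the abstract makes the same declaration. The word non-inferiority is not used again in the sections on sample size, statistical methods or discussion.

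The other elements that fix the hypothesis are these:

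- **Objectives:** the aim is to "examine the effects of the therapeutic VR experience in older people with physical disabilities in LTCF in (1) increasing mental well-being", followed by reducing depressive symptoms and loneliness and raising quality of life and perceived social support.
- **Groups:** "Participants allocated to the control will receive the usual care provided by the LTCF".
- **Relevant concomitant care:** "The participants allocated to the intervention group receive the same usual care provided by the LTCF".
- **Sample size:** a two-tailed t-test on the "difference between two independent means of two groups", with d = 0.407 taken from an earlier VR exercise study, alpha 0.05, power 0.8 and 1:1 allocation. This gives 192 evaluable participants, and 216 after 11.3% attrition.
- **Statistical methods:** GEE with group, timepoint and their interaction, significance level 0.05, intention-to-treat for the primary interpretation.
- **Discussion:** the benefit to residents is made conditional on the intervention being shown effective.

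**The concern.** The framework decides what a result means. Under superiority, p > 0.05 means that a benefit was not shown. Under non-inferiority, the same data might be reported as a success if the confidence interval excludes some tolerated loss. The article declares the second framework and builds everything else on the first.

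The mismatch matters more here because VR is added to usual care. Showing that usual care plus VR is not much worse than usual care alone says nothing about whether well-being rises, which is the first stated objective. The label therefore offers a route to a favourable-sounding conclusion from a null result, and that conclusion would not answer the question the trial was set up to answer.

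**Working it through.** **1. Reproduce the plan's sample size.** Inputs from the Sample size section: d = 0.407, two-sided alpha 0.05, power 0.80, 1:1 allocation, attrition 11.3%.

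- Normal approximation: n per group = 2(1.96 + 0.8416)² / 0.407² = 94.8, so 95.
- Noncentral t: 95.73, so 96 per group and 192 in total. Power at 96 per group is 80.1%.
- One-sided t-test at 0.05: 75.33, so 76 per group. This does not match the plan.
- Attrition: 192 / (1 − 0.113) = 216.5, against the stated 216.

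The stated figure is the two-sided superiority number. The section presents 0.407 as an expected between-group effect, not as a margin.

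**2. Set the elements side by side.**

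| Element | Framework it implies |
|---|---|
| Abstract and Trial design label | Non-inferiority |
| Objectives: improve five outcomes | Superiority |
| Comparator: same usual care in both arms, VR added in one | Superiority |
| Sample size: two-tailed test of an expected difference | Superiority |
| Analysis: GEE at 0.05, intention-to-treat primary | Superiority |
| Discussion: conditional on proven effectiveness | Superiority |

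Nothing in the article reconciles the first row with the others.

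**3. Illustrate what the label could permit.** The margins and the T0–T1 correlation (rho) below are assumptions, because the article gives neither. With equal variances at both timepoints, the group-by-timepoint contrast in SD units has SE = √(4(1 − rho)/96). With a true difference of zero, the probability of concluding non-inferiority at margin M (one-sided 0.025) is Φ(M/SE − 1.96).

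| rho | SE | M = 0.407 SD | M = 0.2 SD |
|---|---|---|---|
| 0.3 | 0.171 | Φ(0.42) ≈ 66% | Φ(−0.79) ≈ 22% |
| 0.5 | 0.144 | Φ(0.86) ≈ 80% | Φ(−0.57) ≈ 28% |
| 0.7 | 0.112 | Φ(1.68) ≈ 95% | Φ(−0.17) ≈ 43% |

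The SE of a simple week-7 comparison, √(2/96) = 0.144, coincides with the row for rho = 0.5.

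**4. What keeping non-inferiority would require.** Using the week-7 comparison that underlies the plan's own calculation, n per group = 2(1.96 + 0.8416)² / M² at a true difference of zero, one-sided 0.025 and 80% power. Evaluable totals for assumed margins are 3,140 (0.1 SD), 786 (0.2 SD), 350 (0.3 SD) and 190 (0.407 SD).

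**The case against.** The strongest reply is that this is a slip in two near-identical sentences. Every working part of the plan agrees on superiority, nothing later uses the label, and no section says that a null result would be called non-inferior. That is a fair account of how the error probably arose, and it explains why the repair is cheap. It does not remove the error: the word names the framework of the primary hypothesis, and the result will be read against it.

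Three stronger readings are tempting, and the documents do not support them.

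- **That non-inferiority cannot be tested because there is no margin.** The article gives none, but the GEE contrast yields a confidence interval that could be compared with one, and a margin may stand in a full protocol or SAP that is not shown. The point rests on the internal contradiction. A margin elsewhere would not cure it, because the objectives and the sample size basis would still be those of superiority.
- **That the trial is too small for any non-inferiority claim.** At a margin of 0.407 SD the requirement is 190 evaluable participants against 192 planned. The accurate statement is only that 0.407 was not chosen as a margin.
- **That the 80% should be set against the 2.5% chance of a false superiority claim.** At a true difference of zero, concluding non-inferiority is a correct decision, so 80% is power, while 2.5% is a type I error. The two are not comparable.

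It is also true that the Statistical methods section lists the model terms without saying which one carries the test. The group-by-timepoint term is the natural reading, not stated text.

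**Conclusion.** The label is wrong as written. The abstract and the Trial design section declare non-inferiority, while the objectives, the add-on comparison with usual care, the sample size, the GEE at 0.05 and the Discussion all describe a superiority trial. This conclusion needs no assumption: it follows from the text and from the sample size, which reproduces as 96 per group with 80.1% power for a two-sided difference test.

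The practical consequence is that a null result could be presented as non-inferior to usual care. How often the data would allow this depends on a margin and a correlation that the article does not give. With 96 per arm and no true effect, the assumed values tried here give about 22% to 95%. That range is illustrative, and the finding does not depend on it. Nothing in the article shows that the investigators intend such a reading.

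**What to change.** Replace non-inferiority with superiority in the abstract and in Trial design. Add to Statistical methods that the primary claim requires the two-sided 5% group-by-timepoint test on WHO-5 to favour VR, and that a non-significant result will not be read as non-inferiority.

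The cost is one word in each of two places and one added sentence. The sample size, data collection and GEE model are unchanged. The Trial status section reports that VR software is still in development and recruitment has yet to start, so the correction can be made before any outcome data exist.

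If non-inferiority is truly intended, a change of wording will not do. The plan would then need a justified margin, a confidence-bound decision rule, a sample size derived from that margin, and objectives rewritten to match.

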## Methods

The Standard Protocol Items: Recommendations for Interventional Trial (SPIRIT) 2013 guideline is followed to structure the report of this trial protocol and the details can be referred to Appendix: SPIRIT checklist [35].

### Study setting

This study will be conducted in the LTCF. Participants will be recruited from residential care homes for the elderly under the governance of the Social Welfare Department in Hong Kong [36]. The list of 171 residential care homes is shown in the Supplementary Document. Invitations will be extended to the residential care homes for the elderly and those who are interested will be invited to join the study. These residential care homes for the elderly provide residential care, meals, personal care, regular basic medical and nursing care, and social support for older people who suffer from poor health or physical/mental disabilities with a deficiency in activities of daily living but are mentally suitable for communal living [37].

### Eligibility criteria

#### Inclusion

Aged 60 years or above;LTCF residents; andPhysical disabilities, as defined by the modified Barthel Index (MBI) score of ≤ 90 (i.e., moderately dependent or worse) [38].

#### Exclusion

Probably dementia, as defined by a Hong Kong version of the Montreal Cognitive Assessment (MoCA) score of < 19 [39];Severe visual impairment, as defined by a lens-corrected visual acuity score of < 6/60 [40];Severe hearing impairment, as defined by failed whispered voice test [41];Bilateral upper limb paralysis, as defined by the Medical Research Council Muscle Power Scale of < 4 [42]; orParticipated in any VR activities in the past 6 months or concurrently.

### Intervention

#### Intervention key elements

As shown in Table 1, the intervention is described in nine key elements. The VR experience includes three therapeutic themes: natural scenery, outdoor leisure, and reminiscence because evidence showed that they are effective to promote mental health in older people [18, 22, 23]. In natural scenery, participants will be exposed to a virtual environment where they can visualize natural elements. In outdoor leisure, participants will be exposed to a virtual environment where they can visualize an outdoor relaxing environment. In reminiscence, participants will be exposed to a virtual environment where they can see old Hong Kong-themed environments.

**Table 1 Tab1:** Intervention key elements

Intervention key elements	Contents
Components	• Natural scenery • Outdoor leisure • Reminiscence
Materials	• VR head-mount device • Tablet computer • Intervention implementation manual
Procedures	• Briefing • VR experience • Post-VR group discussion
Who	• Trained young volunteers
How	• Face-to-face
Where	• Bed or wheelchair in a shared room in LTCF
Duration	• One hour per session ◦ Briefing: 10 min ◦ VR experience: 20 min ◦ Post-VR group discussion: 30 min
Frequency	• 2 sessions per week
Course	• 6 weeks

The VR experience is launched on the participants using all-in-one VR head-mount devices. Tablet computers are used to optimize the settings by the interventionists. The image of each participant’s VR experience can also be mirrored on the tablet computers for the interventionists to monitor the progress of the intervention. A standardized intervention implementation manual depicts all the key steps in guiding the participants to explore the virtual environment.

In each session of the intervention, there are three parts: briefing, VR experience, and post-VR experience group discussion. In the briefing, VR head-mount devices are calibrated and put on the participants. Rules and control commands will also be introduced to participants. In the VR experience, interventionists will guide the participants to explore the virtual environment following a standardized intervention implementation manual. In the post-VR experience group discussion, the interventionists guide the participants to share their experiences (e.g., interesting encounters, difficulties, and associated anecdotes). The interventionists end the session by concluding their shared experiences.

The interventions can be implemented by the interventionists face-to-face with the participants in any room at the LTCF (e.g., activity room, participants’ bedrooms). Participants can join the intervention in a sitting position while they are in their beds or wheelchairs.

Each session lasts for approximately 1 h with 10 min spent on the briefing, 20 min spent on the VR experience, and 30 min spent on the post-VR group discussion. There are two sessions per week. The whole course lasts for 6 weeks and there are a total of 12 sessions.

